### Data Collection

#### Phase 1

After recruitment and enrollment into the study (week 1), nursing students in each semester will be randomized into either the intervention or control group and will be assigned a unique participant code number. The allocation ratio will be 1:1 (intervention or control group), following a simple randomization procedure (Microsoft Excel [Microsoft Corp.] random number table). Research team members involved in data collection will be blinded to the allocation; participants will become aware of their randomization on receipt of an email from the researchers outlining their allocation into the intervention or control group. At this time, students in the intervention group will receive access to the eMAR simulation game approximately 2 weeks in advance of their in-person simulation sessions with the eMAR technology in the CSL. Along with access to the eMAR simulation game, students in the intervention group will also have access to other usual preparatory educational resources related to medication administration, such as a video demonstrating proper administration technique and a PowerPoint presentation on eMAR medication administration. To ensure a consistent duration of game intervention, students will be requested to use the eMAR simulation game for a minimum of 60 min (with no maximum) [29] before conducting their return demonstration of a medication administration using the actual SMART eMAR system in the CSL (starting week 5); analytics software operating in the background of the game will be used to track the average game play duration of participants. Students allocated to the control group will receive the usual preparatory resources related to eMAR medication administration, without access to the eMAR simulation game. At the conclusion of the trial in late October and February (week 9), all participants in the control group will receive access to the eMAR simulation game.

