The duration of the active trial in each academic semester will be approximately 4 weeks, running the months of October and February. The simulated return-demonstration patient scenario that all students will be required to complete involves conducting a baseline physical assessment on a high-fidelity human mannequin simulator, performing the ordered medication administration using the SMART eMAR system, and conducting a patient follow-up assessment and documentation of the encounter in the patient’s clinical record. All participants in the intervention and control groups will receive the same patient and medication administration scenario to maximize contextual internal validity.

Prepost data related to medication self-efficacy and knowledge will be collected through a Qualtrics (Qualtrics Inc.) Web-based survey platform before (week 4) and after the simulated return-demonstration patient scenario (week 8). Cross-sectional survey data will be collected from the intervention group only, immediately after the simulated return-demonstration patient scenario (week 8; Figure 2).

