#### Outcomes

Data will be collected by 4 data collectors (nursing graduate students with clinical backgrounds using eMAR technology) who will observe nursing student participants during their return demonstration of medication administration using the SMART eMAR (weeks 5-8). These data collectors will be trained by members of the research team before the study initiation to ensure the appropriate and consistent use of the checklist to collect participant data. Mock student return demonstrations and related data collection will be conducted to improve interrater reliability; Fleiss kappa coefficients will be calculated and used to further refine interrater reliability of the data collection procedure. A formalized checklist that has been developed and used previously in an adapted form by the research team [20] will be implemented as the primary data collection instrument for phase 1. This data collection checklist will capture the following quantitative data during each participant’s medication administration return demonstration using the SMART eMAR: (1) frequency of deviations from medication administration best practices, (2) number of actual medication errors or near misses generated by the student that violate the various medication best practices and provincial regulatory requirements related to medication administration [30,31], and (3) overall duration of time required by the student to complete the entire medication administration simulated scenario. Secondary outcomes using prepost survey data related to medication self-efficacy and knowledge will be collected using questions modified from previously developed and tested instruments [32,33]. Secondary outcome cross-sectional data will also be collected using questions modified from the Huang et al’s [34] validated instrument that measures motivational (ie, attention, relevance, confidence, satisfaction) and cognitive processing of learning in game-based environments (20 questions, Cronbach alpha=.91). Measurement of motivational and cognitive processes of learning will identify levels of participant motivation related to cognitive load requirements demanded by the eMAR simulation game.

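### Simple randomisation and an unadjusted t test leave test week (weeks 5 to 8) as avoidable noise; the comparison is not biased, and the remedy is cheap

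*Protocol article*

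**What the plan says.** All references are to the protocol article. Under Data Collection, Phase 1, allocation is individual and separate by term: "nursing students in each semester will be randomized into either the intervention or control group". The method is given as "The allocation ratio will be 1:1 (intervention or control group), following a simple randomization procedure", run from a spreadsheet random number table. No balancing by laboratory week or section is mentioned.

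The same section fixes a single test case: "All participants in the intervention and control groups will receive the same patient and medication administration scenario to maximize contextual internal validity". Outcomes places the observation of students "during their return demonstration of medication administration using the SMART eMAR (weeks 5-8", so testing spans four weeks in each semester. How a student is placed in a particular week is not stated.

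Intervention students get the game "approximately 2 weeks in advance of their in-person simulation sessions with the eMAR technology in the CSL" and are asked to play "for a minimum of 60 min (with no maximum". It is unclear whether access opens on one date for all or is timed to each student's own slot.

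Data Analysis, Phase 1, names a Student t test for errors or near misses, deviations and time. It mentions no term for semester or test week. Strengths and Limitations discusses observer effect, rater variability and dose-response, but not knowledge of the scenario passing between classmates.

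**The concern.** Test week may predict the outcomes. The students belong to one cohort and are new to medication administration. Knowing the case beforehand could reduce deviations, errors and completion time. If the game opened on one date about two weeks before week 5, possible play time before the test would run from about 2 weeks (tested in week 5) to about 5 weeks (tested in week 8).

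Simple randomisation fixes neither the arm sizes nor the arm split within a week, and a plain t test leaves any week effect in the residual variance. Students are enrolled before allocation in each semester, so a balanced list is possible. What is at stake is precision and, separately, a contrast that shrinks if the scenario becomes known.

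**Working it through.** **The plan's own figure.** The article gives no figure on test week. Its only relevant number is the sample size: 120 participants, effect size 0.25, power 0.8, two-tailed 5% t test. With 60 per arm and a standardised difference of 0.25, exact power is 0.27, so that figure is not reproduced. This is a separate matter. Here I use a true effect of d = 0.5, close to the 0.52 that 60 per arm detects with power 0.80.

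**Inputs.** From the article: 120 students, two semesters, four test weeks, 1:1 simple randomisation, unadjusted t test. Assumed: 60 students per semester, 15 per week, within-week SD of 1, and a linear improvement from week 5 to week 8 of 0, 0.5 or 1 SD.

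**Chance splits.** Binomial(15, 0.5): one week splits 10:5 or worse with probability 0.302, and 11:4 or worse with 0.118. At least one of eight semester-weeks splits 11:4 or worse with probability 1 − (1 − 0.118)^8 = 0.64. Binomial(60, 0.5): a semester splits 36:24 or worse with probability 0.155. Such a split still keeps 4 × 0.6 × 0.4 = 96% of the efficiency of 1:1.

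**Difference in mean test week.** Weeks coded 0 to 3 have variance 1.25. The between-arm difference has SD of about 2 × √1.25 / √120 = 0.20 week, so a 95% range of about ±0.40 week. In simulation it exceeds 0.25 week in about 24% of trials and 0.5 week in about 1.6%. With a 1 SD trend (0.33 SD per week), the 95% range of the shift in the estimate is about ±0.40 × 0.33 = ±0.13 SD, centred on zero.

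**Variance due to week.** A total trend of T adds T² × 1.25/9. For T = 0.5 this is 0.035, an R² of 0.035/1.035 = 0.03. For T = 1 it is 0.139, an R² of 0.139/1.139 = 0.12. The effective d falls to 0.5/√1.035 = 0.49 and 0.5/√1.139 = 0.47. Exact power for the planned design is then 0.775 with no trend, 0.761 and 0.721.

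**Simulated power at d = 0.5** (60,000 trials per row and design, Monte Carlo error about 0.002). Balanced means within semester and week, with the odd fifteenth place drawn at random. Adjusted means a linear model with semester and week as factors.

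| Trend | Simple, unadjusted | Balanced, unadjusted | Simple, adjusted | Balanced, adjusted |
|---|---|---|---|---|
| 0 | 0.772 | 0.778 | 0.757 | 0.776 |
| 0.5 SD | 0.762 | 0.763 | 0.761 | 0.774 |
| 1 SD | 0.718 | 0.731 | 0.758 | 0.772 |

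Type I error under simple randomisation with the unadjusted test is 0.049 to 0.050, and the mean bias is zero to within simulation error. Balancing without adjusting makes the t test conservative (0.037 at a 1 SD trend), so balance alone gains little power.

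One caution on such simulations. If the odd place always goes to the intervention arm in weeks 6 and 8 and to control in weeks 5 and 7, mean test week differs by 46/30 − 44/30 = 0.067 week. At a 1 SD trend this moves the estimate by 0.022 SD in the intervention's favour. Power for balance alone then reads 0.77 to 0.78, which is an artefact.

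**The case against.** The strongest reply is that simple randomisation is valid. Test week is balanced in expectation, the t test's error rate already covers chance imbalance, and the arms rarely differ by more than half a week on average. All of this stands. A reader might infer that the common scenario protects internal validity only if the arms are evenly spread over the weeks, or that the result would be biased. The documents do not support either. A systematic difference would need slots to depend on arm, for instance slots chosen after the allocation email, and the article does not say that happens.

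A reader might also infer that later students have had more practice. Extra laboratory time is not documented, and Setting and Recruitment describes this as students' first encounter with medication administration. Longer game access follows only if access opens on one date, and it would then vary the dose within the intervention arm rather than unbalance the arms.

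The size of any week effect is likewise assumed, and slot assignment, test dates and disclosure instructions may sit in the full protocol. That limits the point to choices the article does state: simple randomisation, one scenario, a four-week window and a t test.

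Finally, balancing does not stop the scenario from spreading. This is correct, and it is why disclosure needs its own measure.

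**Conclusion.** The point holds as a small, inexpensive improvement. The stated allocation and analysis leave test-week variation in the error term. Compared with the plan, balancing and adjusting together gain about 1 point of power at a 0.5 SD trend (0.762 to 0.774) and about 5 points at 1 SD (0.718 to 0.772), with no loss if there is no trend (0.772 and 0.776). At the 1 SD trend, adjustment alone recovers most of the gain (0.758). At 0.5 SD it recovers none, and with no trend and no balance it costs about 1.5 points.

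These sizes rest on 15 students per week and an assumed linear trend. Neither bias nor an inflated type I error is shown. Disclosure of the scenario is a plausible, unquantified risk that could reach both arms and would mainly narrow the contrast.

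**What to change.** - **Allocation, winter wave.** If the laboratory timetable is known before allocation, replace simple randomisation with a shuffled 1:1 list within each scheduled week or section, with odd places allotted at random. Otherwise shuffle a 1:1 list within the semester. With adjustment, that fallback gives simulated power of 0.766, 0.765 and 0.762 for trends of 0, 0.5 and 1 SD.
- **Analysis, both waves.** Record test week on the checklist and include semester and test week in the model. The Results section says fall data collection has concluded, so fall can be adjusted only if dates were recorded and can no longer be balanced. The achievable power for the whole trial therefore lies between the adjusted columns, about 0.76 to 0.77.
- **Disclosure.** Ask students not to discuss the scenario until week 9, when the trial in that semester ends.
- **Game access.** State whether access opens on one date or relative to each student's own session.

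The cost is a different spreadsheet sort, one checklist field, a few degrees of freedom (four for semester and week as factors), one sentence in the student briefing and one in the protocol. The only real constraint is having the timetable before allocation.

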### Setting and Recruitment of Participants

Two waves of second-year baccalaureate nursing student participants will be contacted and recruited for participation in this proposed study at the beginning of 2 separate academic semesters: wave 1 will commence in September 2017 (fall semester) and wave 2 in January 2018 (winter semester). Due to the size of the second-year nursing student cohort (N=150) and resource limitations of the CSL, only half (n=75) of the students will partake in simulated clinical education in the CSL, per semester (split between fall and winter). Inclusion criteria for this study will be (1) second-year nursing students and (2) partaking in clinical simulated education either in fall 2017 or winter 2018 semesters. Students recruited in this study will not have had previous exposure to medication administration, and this simulated clinical experience will be their first formative interaction with medication administration and the SMART eMAR.

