**Figure 1 figure1:**
[figure not shown]
Screenshot of the electronic medication administration record (eMAR) simulation game’s user interface and various player-manipulable objects.

Before the start of each term, a researcher-led presentation will be delivered outlining the proposed study purpose, methods, and study benefits. Given the typical student enrollment within second year of the BScN program, it is expected that approximately 150 students will fit this inclusion criterion and be eligible for recruitment into the study. Participants will be offered a Can $5 gift card for a coffee shop as a nominal incentive to participate in the study. Due to the high recruitment success rate experienced in the corresponding pilot study completed in April 2016 (25/27, 93% of students sampled) [11], we estimate 120 participants will be recruited. By including at least 120 participants, phase 1 of our study will be able to detect an intervention effect size of 0.25, with a power of 0.8 and a .05 level of significance, based on a 2-tailed *t* test analysis, as calculated by G*Power 3.1 (Heinrich-Heine-Universität Düsseldorf, Germany).

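### Simple randomization is valid here but leaves arm sizes within each semester to chance; splitting each enrolled semester list in half and including semester in the analysis would be a small, free improvement

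*Protocol article*

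**What the plan says.** Under Data Collection, Phase 1, the protocol article sets out when students are allocated: "After recruitment and enrollment into the study (week 1), nursing students in each semester will be randomized into either the intervention or control group". The next sentence gives the method: "The allocation ratio will be 1:1 (intervention or control group), following a simple randomization procedure". The tool is named only as a "Microsoft Excel [Microsoft Corp.] random number table". No blocking or stratification is mentioned. The text does not say whether the random numbers assign students one at a time or order a list that is then divided. Students learn their arm by email.

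Under Setting and Recruitment of Participants there are two waves, fall 2017 and winter 2018, and "only half (n=75) of the students will partake in simulated clinical education in the CSL, per semester". For the total, "we estimate 120 participants will be recruited".

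Under Data Analysis, Phase 1, the comparison of errors or near misses, deviations and duration is a Student t test, with no mention of semester. The Results section reports that fall 2017 data collection has ended.

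**The concern.** In its usual meaning, simple randomization assigns each student independently. The 1:1 ratio is then a probability, and the arms may differ in size overall and within each semester. The main reason to accept this is that the next assignment cannot be guessed when participants arrive one by one. That benefit has little value here, because a whole wave is enrolled before anyone is randomized. A randomly ordered list cut in half would reveal nothing to the people enrolling and would keep the arms equal.

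Two things are at stake, both small. Unequal arms cost some power. And if the share of fall students differs by chance between the arms, any fall/winter difference in outcome adds noise to an unadjusted arm difference.

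**Working it through.** **Inputs.** From the article: total N = 120, two waves, individual 1:1 simple randomization, two-tailed t test at .05. Assumed: 60 students per wave (half of 120; the upper limit is the 75 available); a fall/winter outcome difference of 0.5 SD, for which the article gives no figure.

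**The plan's own figure.** The article says 120 participants "will be able to detect an intervention effect size of 0.25, with a power of 0.8 and a .05 level of significance". Read as a standardized mean difference in a two-sample, two-sided t test, 60:60 gives 27.4% power, so the figure does not reproduce on that reading. That is a separate matter, and equal arms would not repair it. To measure the cost of imbalance I use the difference that 60:60 detects with 80.0% power, d = 0.516, and also show d = 0.25.

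**Arm sizes under a fair coin**, arm size ~ Binomial(n, 0.5):

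| Students | Exactly equal (to within one if odd) | 95% range for one arm | 40:60 or worse |
|---|---|---|---|
| 60 (one wave) | 10.3% | 22 to 38 | 15.5% |
| 75 (one wave) | 18.2% | 29 to 46 | 10.5% |
| 120 (both waves) | 7.3% | 49 to 71 | 3.5% |

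For 60 students, 40:60 means 36:24. At least one of two waves that uneven: 1 − (1 − 0.155)² = 0.286. Both waves exactly 30:30: 0.1026² = 0.011.

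**Power**, noncentral t with noncentrality d × √(n₁n₂/(n₁+n₂)):

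| Split | d = 0.516 | d = 0.25 |
|---|---|---|
| 60:60 | 80.0% | 27.4% |
| Averaged over simple randomization | 79.7% | 27.2% |
| 49:71 | 78.6% | 26.7% |
| 48:72 | 78.4% | 26.5% |

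The average loss is 0.2 to 0.3 points. At the edge of the 95% range it is 1.4 points for d = 0.516.

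**Semester shift.** Shift = (share of fall students in the intervention arm − share in the control arm) × semester difference.

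- The standard deviation of the difference in shares is about √(0.25/60 + 0.25/60) = 0.091. Times 0.5 SD, the typical shift is 0.046 SD, or about 0.05 SD. It is proportional to the assumption: a 0.25 SD semester difference gives 0.023 SD. Its mean is zero.
- One uneven wave, fall 36:24 and winter 30:30: (36/66 − 24/54) × 0.5 = 0.05 SD.
- Two waves uneven in opposite directions, 36:24 and 24:36: (0.6 − 0.4) × 0.5 = 0.10 SD. Two opposite splits at least that uneven have probability 2 × 0.0775² = 1.2%. A shift of 0.10 SD or more arising in any way has a 3.5% chance.
- For comparison, the standard error of the arm difference at 60:60 is √(2/60) = 0.18 SD.

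**The case against.** The strongest reply is that nothing in the sentence is wrong. An allocation ratio is the intended assignment probability, simple randomization at 0.5 has that ratio, and the article never promises equal counts. This stands. A reader might infer that the stated 1:1 is contradicted or not delivered by the method; the document does not support that.

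A reader might also infer confounding by semester. That is not supported either: the shift averages zero over randomizations and is random error that the standard error of an unadjusted test already reflects. A 0.10 SD shift is an unfavorable case resting on an assumed semester effect, not an expected result.

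The Excel wording is compatible with sorting the list and cutting it in half, so the trial may already have equal arms. This also stands. In that case the label is what needs correcting, because a fixed split is restricted randomization.

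An analysis plan not shown may include semester, and covariates are often left to it. The missing term is therefore no error in the article. If semester is adjusted for, the shift argument falls away and the small power cost remains.

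Finally, the fall wave cannot be re-randomized, so the allocation change can help only a wave not yet randomized. What survives is that each semester's list is available before randomization, so the more balanced procedure has no drawback.

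**Conclusion.** The point stands as a minor, optional improvement. The randomization as described is valid and unbiased, but it does not guarantee equal arms within a semester. With 60 students per wave, a 36:24 or worse split has a 15.5% chance in one wave and 28.6% in at least one of two. With 75 per wave the one-wave chance is 10.5%. The consequences are slight: a fraction of a power point on average, and a typical shift about a quarter of the standard error (0.046/0.18) if semesters differ by 0.5 SD.

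These figures rest on three assumptions: independent one-by-one assignment, equal waves, and an analysis without semester. They do not threaten the trial's validity or conclusions.

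**What to change.** 1. State how the Excel random numbers were used. If the list was sorted and split, replace the label simple randomization.
2. For any wave not yet randomized, wait until that semester's enrolled list is complete, sort it by a random number in the same Excel file, and assign one half to each arm. A list of 60 gives 30:30; an odd list such as 75 gives 37:38, and chance should decide which arm takes the extra student.
3. Describe this as randomization stratified by semester with equal arms.
4. Include semester as a factor in the between-arm analysis of both waves. This applies to the fall data too, whose allocation can no longer change.

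The cost is a sentence or two of text and one extra term in the model. The tool and the workload stay the same.

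### Controls share a semester with classmates who hold the game, and the stated exposure measures would not show whether controls used it, so a null result would be hard to interpret

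*Protocol article*

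**What the plan says.** All references are to the protocol article.

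- **Unit of allocation.** Under Data Collection, Phase 1, "nursing students in each semester will be randomized into either the intervention or control group". The method is individual: "The allocation ratio will be 1:1 (intervention or control group), following a simple randomization procedure".
- **Setting.** Under Setting and Recruitment of Participants, "only half (n=75) of the students will partake in simulated clinical education in the CSL, per semester", out of a second-year cohort of 150.
- **Timing.** Intervention students get the game roughly 2 weeks before their laboratory sessions (Data Collection, Phase 1). Return demonstrations are observed over weeks 5-8 (Outcomes). Controls get the game at week 9. No withdrawal of the intervention arm's access during testing is described.
- **Control condition.** "Students allocated to the control group will receive the usual preparatory resources related to eMAR medication administration, without access to the eMAR simulation game".
- **Exposure measurement.** "analytics software operating in the background of the game will be used to track the average game play duration of participants". The cross-sectional survey on the game goes to the intervention arm only. The surveys at weeks 4 and 8, which both arms complete, are described as covering self-efficacy and knowledge.
- **Other contact with controls.** Phase 2 interviews about 20 students from both arms at week 9. The topics named are the core phase 1 variables and the usability, design and experience of the game.
- **Limitations.** The Strengths and Limitations section names an observer effect, variability between observers and the difficulty of a dose-response reading. It does not name contamination.

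**The concern.** Students are told their arm by email, and a presentation before each term explains the study's purpose and methods. Controls can therefore be expected to know that a game exists and that other students in the same laboratory semester have it. All of them face the same return demonstration, which gives a reason to look for extra preparation. Nothing described would record a control who played or watched the game with a classmate.

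If the game works, such use makes controls resemble the intervention arm and shrinks the differences in errors, deviations and completion time. Research question 1 asks whether use of the game improves administration safety. Without a record of control use, a null result could mean that the game does little, or that the comparison was diluted. The knowledge part of research question 2 is open to the same problem.

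**Working it through.** **1. What each stated source could show about control use**

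| Source | Who is covered | Could it show control use? |
|---|---|---|
| In-game analytics | Those playing on granted access | No. The article does not say how access is granted. Borrowed play would at most add to the holder's time, watching leaves no trace, and an average does not show who played |
| Week 8 game survey | Intervention arm only | No |
| Week 4 and week 8 surveys | Both arms | Not as described: self-efficacy and knowledge only |
| Week 9 focus groups | About 20 students, both arms | Possibly for a few; no stated question on sharing |

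**2. The plan's own power figure**

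The article states "we estimate 120 participants will be recruited" and that phase 1 "will be able to detect an intervention effect size of 0.25, with a power of 0.8 and a .05 level of significance". It names a two-sided t test. Simple 1:1 allocation of 120 gives about 60 per arm. For an independent two-sided t test (noncentral t):

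- d = 0.25 needs about 253 per arm; 60 per arm gives 27% power.
- 60 per arm reaches 80% power at d of about 0.516.

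The stated figure does not reproduce on this reading, nor as a paired two-sided test or with 0.25 taken as Cohen's f for two groups (both need 128 in total). That is a separate matter. It is relevant here because it leaves no reserve to absorb dilution, and because a dilution example that starts near 80% power needs an effect larger than the stated one.

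**3. Dilution**

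Let c be the share of controls exposed and e the share of the full effect they gain. Then

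observed d = true d × (1 − c × e).

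Neither c nor e is in the document. Take d = 0.52 as an assumption, close to what 60 per arm can detect; power is then 80.6% with no leakage. Two-sided .05, 60 per arm:

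| c | e = 0.5: diluted d | Power | e = 1: diluted d | Power |
|---|---|---|---|---|
| 10% | 0.52 × 0.95 = 0.494 | 76.5% | 0.52 × 0.90 = 0.468 | 72.0% |
| 20% | 0.52 × 0.90 = 0.468 | 72.0% | 0.52 × 0.80 = 0.416 | 61.8% |
| 30% | 0.52 × 0.85 = 0.442 | 67.0% | 0.52 × 0.70 = 0.364 | 50.7% |

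At the stated 0.25, read as a standardised mean difference, power is 27.4% with no leakage and 23.1% at c = 10%, e = 1.

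**4. What a complier-average estimate could add**

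With arm as instrument, the estimate is the as-randomised difference divided by the between-arm difference in the share exposed. If every intervention student uses the game and a share c of controls does, that divisor is 1 − c. The estimate and its standard error are rescaled together, so power is not recovered. If only winter exposure is known, the analysis has about 120 / 2 / 2 = 30 per arm, assuming recruitment splits evenly over the two waves. At d = 0.52 with no leakage, 30 per arm gives about 51% power.

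**The case against.** The strongest reply is that this rests largely on silence. An article condenses a full protocol, and login rules, email wording and single survey items are what it would leave out. Each participant has a unique code and play is tracked in the background, so access may already be tied to a person. This stands as far as access control goes, and no gap there is claimed. But the article itself states the unit of randomisation, the exposure measure, who receives the game survey and the limitations, and the point concerns those.

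A reader might infer that controls did use the game, or that leakage would go entirely unseen. The documents support neither. They report no sharing and no rate, and they do not say that each semester's students form one class or how closely the arms mix before testing. The focus groups could bring some sharing to light, although they reach about 20 students and have no stated question on it.

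A reader might also take the larger power losses as the expected ones. They require every exposed control, including one who only watched, to gain the full effect. With modest exposure and partial benefit the loss is a few points.

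Finally, if the game helps, leakage biases towards no difference and does not manufacture a benefit. Individual randomisation is defensible with about 75 students per wave. Both points stand. They argue for measuring exposure, not for changing the design.

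**Conclusion.** The point holds in a limited form. Individual randomisation among students of the same laboratory semester, with the game in classmates' hands before and during testing, makes control exposure possible, and the stated measures would not record it. If the game works, any exposure moves the differences towards zero and makes a null result hard to interpret.

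The size is unknown. In the illustration, power falls from 81% to 77% in the mildest case and to 51% in the most severe, given the assumed d, c and e; none of the three comes from the document. The conclusion also assumes that the full protocol adds no question to controls about game use. This is a cheap improvement to what the trial can conclude, not a flaw that invalidates the design.

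**What to change.** **For the winter wave:**

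- In the allocation email, ask intervention students not to share the game before the trial ends.
- Add one item to the existing week 8 survey, for both arms: before the return demonstration, did you play the eMAR game, did you watch someone else play it, and for about how many minutes each? Record playing and watching separately, so that a brief look is not counted like the requested 60 minutes. Asked after scoring, it does not prompt controls.

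**For the analysis and report:**

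- Keep the as-randomised comparison as the main analysis, and report the share of controls exposed.
- The Results section says fall 2017 data collection has concluded. State fall control exposure as unknown unless those students can still be asked.
- List contamination among the limitations.
- A complier-average estimate is optional and should be labelled exploratory, for the reasons in the working.

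The cost is one sentence in an email, one survey item and a few lines of reporting, with no extra participants or staff. The downside is that self-report may under-count exposure, so the reported share is better read as a lower bound.
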